## Abstract

**Background:**

For therapists, the spoken word of their patients is among the most important foundations for clinical assessment. At the same time, it is hardly possible to monitor patients continuously and closely in sufficient numbers, for example, to ongoingly assess the risk of suicide in therapeutical conversations. Natural Language Processing (NLP) involves the use of Artificial Intelligence (AI) to analyze human language. Combining it with AI speech processing methods, we obtain multimodal methods which can automatically process large volumes of speech and language data to extract diagnostic information and therefore support individualized treatment plans. Thus, in NLP/multimodal methods, we see the opportunity to significantly improve patient care.

**Methods:**

The SPEAK-SAFE project, implemented by clinicians and clinical researchers from the University hospital in Frankfurt in collaboration with the AI experts from the TU Darmstadt, aims to create the first German psychiatric corpus for evaluating and developing multimodal and NLP models to optimize diagnostic processes in psychiatric, psychosomatic, and psychotherapeutic care. Therefore, we will collect therapist-patient dialogues during therapy sessions. This sensitive data necessitates robust privacy. To meet this requirement, all collected data is pseudonymized, to ensure that no personal data is part of the evaluation and training of the AI models.

**Discussion:**

During the implementation of our research project, we were faced with challenges regarding the security of patient privacy and the technical implementation of therapy recordings toreassure sufficient data quality for the data analysis. Therefore, in addition to improve the suicidality prediction with multimodal methods we will develop an end-to-end-workflow for further AI-research in the clinical context.

**Clinical Trial Registration**: https://drks.de/search/de/trial/DRKS00027878, identifier DRKS00027878.

## Introduction

### Background and rationale

According to the Federal Statistical Office of Germany suicide led to more than 10,000 deaths in 2024 (1) and is the most common cause of death among young people between the age of 10–25 in 2023 (2). In most suicide cases, individuals suffered from mental health disorders with rates ranging from 87,3% (3) up to 96,8% (4). Preventing suicides or suicide attempts is the goal of every psychiatric patient treatment and requires an ongoing suicide risk assessment. Thereby, most people committing suicide consult clinicians in the days or weeks prior to death (5, 6). However, predictive markers are currently not sufficiently able to predict suicide risk. Clinicians rely on spoken self-reports to gain insights into the patient's psychological state. Speech comprises a variety of aspects which carry information about someone's psychological state, like e.g., the content, speaking rhythm, loudness, pitch, pace, or coherence (7, 8). The diversity of content-related linguistic features that have been shown to be relevant for diagnostic assessment (9) and for the identification of suicidal ideation (10) is so extensive that a comprehensive evaluation of these features during an ongoing clinical conversation is unrealistic. It is therefore plausible that, along other factors, this linguistic complexity contributes to the limited consistency observed in suicide risk assessments (11). Further, some of the aspects of speech are subtle and hard to assess reliably by a human listener during a conversation, like e.g., jitter, shimmer, or harmonics-to-noise ratio, but important for the understanding of psychiatric illness' like depression (12). Thus, to implement meaningful preventive measures, there is an urgent need for methods able to assess all important predictive markers related to suicide risk and mental disorders in general. Recent advances in Natural Language Processing (NLP), a field within artificial intelligence (AI), show promising results in mental disorder detection and an upward trend within this research area (13). Within NLP methods, linguistics and computer science enable large-scale analysis of language which are also applicable to the clinical psychological practice, where language plays a crucial role in patient care. NLP can be applied to various kinds of text data like social media posts (14–16), interviews (17, 18), and clinical notes (7, 19, 20). For the clinical psychiatric context, studies show promising results for the appliance of NLP methods. Regarding the field of suicide and suicide risk research, NLP models can successfully identify patients who have attempted suicide (20), predict suicidal ideation (17), and distinguish between suicidal and non-suicidal teenagers (21). Furthermore, suicidal language appears to be a stable classifier when compared to standard measurements. This stability is evident as suicidal language persists for up to 30 days after discharge from care, even when responses to other measurements change (18). Accordingly, there are multiple NLP-based methods which enable the exploration of previously unexamined linguistic features.

The aforementioned approaches have been somewhat overshadowed since the introduction of the Transformer architecture (22) and its fast development and huge impact, the evaluation of speech data has totally changed. Models have grown tremendously in a short period of time e.g., GPT3 is more than 100 times bigger than its predecessor GPT2 (23). Due to this rapid development, it is now possible to use even large amounts of speech data, such as clinical interviews, for evaluation with large language models (LLMs). Modern LLMs are not only ideal for general purposes, they also show capabilities when it comes to specific tasks in the domain of mental health (24). It could be demonstrated that LLMs like GPT-3.5 and GPT-4 are able to correctly identify patients with depression. However, they are known to show a considerable language bias and due to their nonspecialized training data, they are better at identifying control participants which could narrow their direct applicability for mental health applications (25). Models specialized on medical knowledge like Med-PaLM-2 can demonstrate human-like performance when predicting PHQ8 scores used for the assessment of the severity of depression (26). Besides spoken language many studies utilize written language like social media data and show promising results even with simple prompting strategies (27). Modern LLMs capabilities go way beyond this and offer numerous applications in addition to those mentioned before. Other studies indicate their usefulness in giving treatment suggestions (28) or creating simulated patients for psychotherapy training (29).

Apart from the content it is also important to take acoustic features accompanying the linguistic content in speech, also called prosodic and intonational features into account. These features are beyond the content related aspects of speech like phonemes and comprise patterns of pitch, duration, intensity, and rhythm, but are important in conveying meaning, emotion and nuance in speech (30). Recent studies focusing on acoustic features (31, 32) confirm that detection and severity assessment of mental health conditions like depression can be achieved with high accuracy based solely on acoustic information, demonstrating that vocal markers provide a reliable proxy for underlying affective states. In addition to research focusing on one modality, there are studies that consider both linguistic and acoustic features in a single study (33).

With multimodal models, large scale language and acoustics data can be processed simultaneously to get a better prediction of e.g., suicidality (34) and depression (35). Those multifaceted insights can greatly enrich existing knowledge about diseases like depression or schizophrenia and thus improve patient diagnosis and care. Moreover, a multimodal approach enables a much more realistic evaluation of speech data sets and is therefore useful in many counseling situations.

## Objectives

Considering the lack of linguistic diversity in datasets with a clear bias towards English (13, 36) and social media data (24), we see an urgent need for further non-English speech datasets (37). To this day there is no sufficiently large German speech corpus from severely ill psychiatric patients. There have been several valuable efforts to advance the analysis of language in the context of psychotherapy and mental health within German-speaking populations. However, existing studies have primarily focused on outpatient samples with milder symptom severity (38) or relied on relatively small datasets (39). While these contributions are undoubtedly significant, they nevertheless leave an important gap regarding large-scale datasets from more severely affected patients in inpatient settings. Existing corpora, such as the Research and Teaching Corpus of Spoken German (FOLK) (40), are not specifically designed to meet the needs and peculiarities of psychiatric and psychotherapeutic contexts, thus limiting their utility for NLP and multimodal methods in these fields. Even from a global perspective, language data sets are rather rare compared to the multitude of existing languages (41).

We therefore aim to generate a large enough trans-diagnostic collection of audio data of hospitalized patients and patients treated in our outpatient clinic. A study by Parola et al. (42) has shown several language specific differences regarding reduced semantic coherence in schizophrenia, which indicates a limited generalizability of speech patterns across different languages.

With our study, we aim to fill this gap by applying recent advances in NLP and multimodal methods. Our goal is to help identify non-explicit content language patterns in clinical patients, which can serve as prognostic markers specifically for the German language. Thus, our primary aim is to assess the suicide risk in patients with depression, bipolar disorder, and psychotic disorders, such as schizophrenia, schizoaffective disorder and acute polymorphic psychotic disorder (according to ICD-10), as well as the psychopathological development (Clinical Global Impression, CGI). As a secondary outcome we want to assess the overall psychopathological condition of the patients. This includes standardized and validated questionnaires comprising the clinician's impression of the patients general psychosocial functioning (Global Assessment of Functioning, GAF), suicidal symptoms (Depressive Symptom Index—Suicidality Subscale, DSI-SS) and suicidality (Suicidal Scale of the Mini-International) as well as electronic health records (EHR) of the patient's psychopharmacological medication. Generally, the standardized text of the patient's EHR will be accessible for the text-based analysis. These will be supplemented by the standardized assessment through a clinician, which will be used as the gold standard for comparison with the AI analysis.

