**Figure 1 F1:**
[figure not shown]
Schematic depiction of data collection and analysis workflow.

Both, audio track and therapy transcript have to be pseudonymized to ensure data privacy. The sessions are transcribed to text with the freely available software WhisperX (57). In order to pseudonymize the data, the members of the study team listen to the therapy session and check the transcript at the same time. In this way it is not only possible to delete personal data but also keep track of transcription errors. Furthermore, this also enables the correction of errors in speaker diarization which will be relevant for data analysis. Transcripts are also edited according to predefined rules to ensure consistency, including standardized notation for stuttering and speech disfluencies, clear indication of overlapping speech, flagging of incomprehensible sections, and documentation of interruptions such as third parties entering. By doing this we are left with not only a pseudonymized audio track but also with a high quality pseudonymized and diarized transcript. Afterwards, the transcripts are ready for use with e.g., locally operating LLMs to assess their capability to distinguish between patient groups and evaluate symptom severity. The audio tracks are ready for feature extraction with the open-source toolkit openSMILE (56). Extracted audio features will serve as the basis for subsequent calculations, e.g., correlations with specific symptoms as well as general severity scores. Details of the unimodal and multimodal analyses are provided in the Statistical Methods section.

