### Confidentiality

A dedicated data security concept for this study was developed in close collaboration with the local data protection officer, fully compliant with the EU General Data Protection Regulation [GDPR, Regulation (EU) 2016/679] and the German Federal Data Protection Act (Bundesdatenschutzgesetz, BDSG). The measures ensure both technical and organizational protection of personal data throughout the project. Key provisions include strict pseudonymization and, where feasible, anonymization of all personal data before processing. Access to sensitive data is restricted through a role-based authorization system, and all project staff are trained in privacy and IT security procedures. Data transfers are conducted via encrypted communication channels (TLS/SSL), and stored data is protected using state-of-the-art encryption algorithms. Routine system audits, monitoring, and regular penetration testing are implemented to detect and mitigate vulnerabilities. Redundant backups are encrypted and stored in physically secure environments, with access strictly controlled. Detailed data usage logs and audit trails are maintained to record all data access, modifications, and deletions. The network infrastructure is protected by firewalls and intrusion detection systems, and written informed consent is mandatory for all data subjects. These measures collectively ensure the confidentiality, integrity, and availability of research data, safeguarding data subjects' rights according to EU and German law. Specifically, we implemented the following measures to ensure data security. For every enrolled patient a participation ID will be generated via SecuTrial, a software for managing and conducting clinical trials, offering data collection, management, and analysis with high security and quality standards. One secured document which is saved locally in the University hospital Frankfurt contains the assigned patient identities to the SecuTrial-IDs. All confidential data will be stored exclusively in the university hospital Frankfurt. The questionnaire data will be transferred to SecuTrial and stored under the assigned participant ID. The raw audio files and their transcripts are then pseudonymized by a member of the study group. This involves deleting elements that can be clearly attributed to the patient or the clinician, such as names, addresses, institutions, or other personal information. All files are pseudonymized in compliance with data protection regulations and stored under the assigned participants ID. Password-protected Excel file (256-bit key) with the association of real names is stored in the hospital network. Only designated study personnel with identifiable names have knowledge of this password. Access to the system is logged in a log file.

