
## Statistical methods

### Statistical methods for primary and secondary outcomes

We will employ a zero-shot prompting approach with OpenAI's recently released GPT-OSS (Generative Pretrained Transformer—Open Source Software) series models, which are available under the permissive Apache 2.0 license and have demonstrated strong performance on reasoning tasks relevant to clinical assessment. We have selected these models for several methodological and practical reasons:

First, their open-weight nature ensures full transparency and reproducibility of our analyses. Second, their mixture-of-experts architecture enables efficient deployment on clinical infrastructure with limited computational resources. Third, their documented performance on complex reasoning tasks, including healthcare-related queries, makes them well-suited for psychiatric assessment applications.

Our primary analytical comparison will involve two model sizes from the GPT-OSS family: GPT-OSS-120B (116.8 billion total parameters with 5.1 billion active parameters per token) and GPT-OSS-20B (20.9 billion total parameters with 3.6 billion active parameters per token) (58). This comparison directly addresses a critical question for clinical deployment: whether larger, more capable models provide sufficient performance advantages to justify their greater computational demands, or whether smaller, more efficient models can achieve comparable diagnostic accuracy. The GPT-OSS-120B model has been shown to achieve near-parity with state-of-the-art reasoning models on standard benchmarks while running efficiently on a single 80GB GPU, whereas GPT-OSS-20B delivers comparable performance to advanced compact models while requiring only 16GB of memory, making it feasible for deployment on standard clinical workstations or even edge devices.

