The SPEAK-SAFE study utilizes both structured (questionnaires) and unstructured (conversation recordings) data. While structured data offers standardized, easily quantifiable information, unstructured data provides rich, contextual insights into patient-therapist interactions (68). Our decision to focus on conversational data stems from its potential to capture subtle linguistic markers of mental health states that may not be evident in structured assessments. Our aim is to predict occurring changes in the structured data, what we consider as ground truth, by using the rich, unstructured speech data.

A limitation of the current study design is the lack of long-term follow-up to assess the predictive accuracy of the NLP/multimodal model over time. This has been done so far by only few studies (36). While our approach provides valuable insights into immediate risk assessment, the dynamic nature of mental health conditions necessitates longitudinal evaluation. Future research should incorporate extended follow-up periods to validate the model's long-term predictive capabilities and assess its utility in tracking treatment progress.

The use of AI in mental healthcare raises important ethical considerations. Potential biases in NLP/multimodal models, particularly regarding cultural and linguistic diversity, must be carefully addressed (69). Moreover, the integration of AI-based tools in clinical decision-making necessitates a balance between technological assistance and human clinical judgment. Our study emphasizes the importance of human oversight in interpreting AI-generated insights, recognizing that these tools should augment rather than replace clinical expertise.

The SPEAK-SAFE study has significant potential to enhance mental health care. By providing clinicians with AI-assisted risk assessment tools, we aim to improve the accuracy and efficiency of suicide risk evaluation (34). This could lead to more timely interventions and personalized treatment strategies. However, the successful integration of such tools into clinical workflows requires careful consideration of user acceptance, training needs, and potential impacts on the therapeutic relationship.

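### The text arm has no analysis that separates non-explicit language patterns from explicit talk about suicide, so its accuracy supports detection but not, by itself, the stated marker goal

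*Protocol article*

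**What the plan says.** The goal, in the Objectives section of the protocol article: "Our goal is to help identify non-explicit content language patterns in clinical patients, which can serve as prognostic markers". German is named as the target language. The next sentence gives the primary aim as assessing suicide risk and psychopathological development.

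The material, in the Abstract (Methods): "Therefore, we will collect therapist-patient dialogues during therapy sessions". These are routine sessions (Intervention description).

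What is removed, under Confidentiality: "This involves deleting elements that can be clearly attributed to the patient or the clinician, such as names, addresses, institutions, or other personal information". The other edits, described under Data management, are notation for disfluencies, overlaps, unintelligible stretches and interruptions.

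The use of the transcripts, under Data management: "Afterwards, the transcripts are ready for use with e.g., locally operating LLMs". Their purpose there is to see how well the models separate patient groups and rate severity. The method, under Statistical methods: "We will employ a zero-shot prompting approach". The text results are judged by classification accuracy, suicidality detection, correlation with clinical scales, sensitivity, specificity and predictive values. Tiers 1 and 2 vary model size and temperature. Tier 3 averages the text and acoustic predictions and compares the result with the better single modality.

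**The concern.** The goal concerns patterns that are not explicit in content. The input to the text models is ordinary therapy dialogue, in which a patient may say directly that he or she is suicidal. A model that merely reads such a statement and a model that picks up a subtle linguistic pattern are scored identically, and nothing in Tiers 1 to 3 tells them apart. The expert reference rater listens to the same recordings, so an explicit disclosure can drive both the reference rating and the prediction.

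At stake is the interpretation of the main text result. High sensitivity could be reported as evidence for a non-explicit German-language marker when it shows only that disclosures are readable. Fusion inherits the problem. If explicit content lets text dominate, the acoustic contribution may look small overall even if it matters in sessions without disclosure, and no such split is planned.

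**Working it through.** **1. Goal against analysis.** For accuracy to bear on non-explicit patterns, the plan would need at least one of the following.

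- Explicit passages removed from the input: only identifying elements are deleted (Confidentiality).
- Explicit content as a factor or stratum: the text factors are model size and temperature (Tiers 1 and 2), and Tier 3 adds modality.
- An output showing which pattern drove a prediction: zero-shot prompting scored by accuracy measures gives none.
- An explicit-content-only baseline to beat: none is described.

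None is present for the text arm or for fusion. The acoustic arm differs. The Introduction describes prosodic features as lying outside content, and Tier 1 regresses clinical scores on named acoustic features independently of text.

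**2. The article's own figures.** The sample size does not enter this point, but it reproduces: an exact two-sided binomial test with n = 162, null 0.5, alternative 0.5 + 0.11 = 0.61 and limits 68 and 94 gives alpha 0.0491726 and power 0.8046757, as stated.

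The Discussion cites a study of 100 admission notes with accuracy 87.5%, sensitivity 83.0% and specificity 91.8%. These agree with each other if a share p of notes is positive, with 0.830p + 0.918(1 − p) = 0.875, so p = 0.043/0.088 = 0.49. The false-positive rate is 1 − 0.918 = 0.082.

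**3. What an explicit-only reader could score.** Let e be the share of suicidal sessions containing explicit talk. The documents do not give e. Suppose a reader flags every such session and flags all others at the background rate of 0.082:

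sensitivity = e + (1 − e) × 0.082

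| e | Sensitivity |
|---|---|
| 0.50 | 0.50 + 0.50 × 0.082 = 0.541 |
| 0.70 | 0.70 + 0.30 × 0.082 = 0.725 |
| 0.81 | 0.81 + 0.19 × 0.082 = 0.826 |

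Setting sensitivity to 0.830 gives e = (0.830 − 0.082)/0.918 = 0.815.

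**4. The same on the accuracy scale.** Take balanced classes, as in the Sample size section, and let the reader flag a share e of suicidal sessions with specificity s. Accuracy is 0.5e + 0.5s. For e from 0.6 to 0.9 and s from 0.90 to 1.00 it runs from 0.5 × 0.6 + 0.5 × 0.90 = 0.75 to 0.5 × 0.9 + 0.5 × 1.00 = 0.95. The article's planning accuracy of 0.892 lies inside that range.

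**5. How many sessions would carry the marker question.** With 162 analysable sessions, half of them suicidal (assumed), there are 81 suicidal sessions, of which 81(1 − e) have no explicit talk. The 95% half-width for a sensitivity near 0.5 is 1.96 × √(0.25/n).

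| e | Suicidal sessions without explicit talk | Half-width |
|---|---|---|
| 0.50 | about 40 | 0.155 |
| 0.70 | about 24 | 0.200 |
| 0.81 | about 15 | 0.253 |

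This treats sessions as independent. With up to five sessions per patient, the intervals would probably be wider.

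**The case against.** The strongest reply is that detection is the operative aim. The primary aim is to assess suicide risk, the Outcomes section compares the model with physicians, and the listed outcomes are classification, suicidality detection and severity prediction. Explicit talk is legitimate evidence for all of these. This stands, and the full-transcript result should remain the detection result. It does not remove the mismatch with the goal stated one sentence earlier, which the text arm does not address.

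A second reply is that an article may leave the prompt and input to a fuller document. That is fair for prompt wording. But the article sets out its analysis strategy down to temperature and sampling threshold and presents it as closing off post-hoc flexibility. A masked analysis is not among the analyses it lists.

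Several stronger readings are tempting, and the documents do not support them:

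- A reader might infer that the models read the therapist's questions. The article does not say whether therapist turns enter the prompt. Transcripts are diarized, so patient-only input is possible, though it would still hold the patient's own explicit statements.
- A reader might infer that the study as a whole cannot serve its goal. The Tier 1 acoustic regression uses features outside content and can partly serve it.
- A reader might infer that every reference measure echoes what was said in the session. Patients also complete the DSI-SS and BDI-II at each recorded session, and the MINI suicidality scale at the first.
- A reader might take 83.0% and 91.8% as this study's expected performance. They come from a different, fine-tuned model applied to admission notes.
- The Discussion's reference to the "potential to capture subtle linguistic markers of mental health states that may not be evident in structured assessments" contrasts speech with questionnaires, not explicit with non-explicit speech, so it is only weak support.

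The arithmetic also treats suicidality as binary, whereas the expert rates it in five stages. A suicide disclosure does not settle diagnostic classification or general severity.

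**Conclusion.** The point holds for suicidality in the text arm and in the fusion built on it. Followed exactly, the plan gives a text result that supports detection from the session transcript and does not by itself support a claim of non-explicit markers. The acoustic regression in Tier 1 is not affected, and neither is the sample size.

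The size cannot be fixed from the documents. The sensitivities of 54%, 72% and 83% assume explicit-talk shares of 50%, 70% and 81%, perfect recognition of explicit talk, a binary outcome and a borrowed background rate of 8.2%. They show that good performance is possible with no non-explicit marker, not that this will happen. The change should be made because the interpretation of a headline result depends on it.

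**What to change.** During the planned listen-and-check pass, tag explicit mentions of suicide, death wish or self-harm, and the related therapist questions, under a written definition. Then pre-specify the following:

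- a secondary rerun of the four text conditions on patient turns only, with tagged passages removed;
- text, acoustic and fusion performance for suicidality, reported separately for sessions with and without explicit talk, with confidence intervals because the second group may be small;
- a statement that any non-explicit language-marker claim from text rests on that result only, while the full-transcript result stands as the detection result.

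If this is not done, reword the goal in Objectives as detection of suicidality and severity from full session transcripts.

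The cost is somewhat longer editing and one more inference run. About 200 sessions of 30 to 60 minutes come to 100 to 200 hours of audio, which staff are already to hear in full, so tagging adds to an existing task. The marker claim will rest on a less favourable and less precise figure.
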